## Abstract

**Background:**

A majority of stroke survivors present with cognitive impairments. Attention disturbance, which leads to impaired concentration and overall reduced cognitive functions, is strongly associated with stroke. The clinical efficacy of acupuncture with Baihui (GV20) and Shenting (GV24) as well as computer-assisted cognitive training in stroke and post-stroke cognitive impairment have both been demonstrated in previous studies. To date, no systematic comparison of these exists and the potential beneficial effects of a combined application are yet to be examined. The main objective of this pilot study is to evaluate the effects of computer-assisted cognitive training compared to acupuncture on the outcomes of attention assessments. The second objective is to test the effects of a combined cognitive intervention that incorporates computer-assisted cognitive training and acupuncture (ACoTrain).

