Acupuncture is one of the main modalities of treatment in Traditional Chinese Medicine (TCM) and has a practical history of more than 2000 years in China [15]. A recent meta-analysis [16] was conducted to evaluate the efficacy of acupuncture on cognitive impairment (function) after stroke. Twenty-one trials with a total of 1421 patients were included. The cumulative findings suggest that acupuncture has positive effects on cognitive function after stroke. According to TCM theory of acupuncture, the Du meridian plays an important role in treating attention problems [17]. Baihui (GV20) and Shenting (GV24) are two main acupoints from the Du meridian which are believed to activate the spirit. Previous studies with experimentally induced cerebral ischemia injuries in rodents [18, 19] showed improved learning and memory abilities after 4 weeks (five times per week, 30 minutes per time) of Baihui (GV20) and Shenting (GV24) acupuncture treatment. However, the existing literature of the effects of acupuncture on cognitive impairment after stroke describes general cognitive functions and do not provide sufficient evidence as to how acupuncture could improve attention deficits after stroke.

The aims of our study are: (1) to observe the effect of acupuncture combined with RehaCom training on cognitive dysfunction (in particular attention disturbances) after stroke, and (2) to test efficacy compared to conventional treatment combined with acupuncture or conventional treatment combined with RehaCom training.

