### Sample size

The international setting is thought to increase the generalisability of the study results, as the study sample will include patients with different cultural background. However, it is also expected that high heterogeneity regarding affected cortical areas and functional ability within the study groups of stroke patients will occur. The number of participants will therefore not suffice to conduct a full-scale study but are thought to provide a basis for estimation of the effects and planning of a larger follow-up study, if proven feasible.

The aim is to recruit 20 patients per clinic (N_total_ = 60). The results will be used to compute sample size and conduct a power calculation to plan the full-scale follow-up study.

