### Interventions

All study interventions are described in Table 2 using the Template for Intervention Description and Replication checklist and guide, known as TIDieR. Patients will be evenly allocated to CaCT, AP, or ACT. All groups will additionally receive conventional neurorehabilitative treatment as prescribed by each clinic. The experimental intervention of this trial will be added to the existing therapy plan as a daily treatment of 30 minutes for 4 weeks (Monday to Friday). Every treatment will be documented on the therapy documentation sheet (standardised for each trial centre).

**Table 2 Tab2:** Description of study interventions based on the TIDieR template^*a^

Item	Computer-assisted cognitive training	Acupuncture	ACoTrain
1 Short name	Ca CT	AP	ACT
2 Why	Main objective is to evaluate the effects of computer-assisted cognitive training CaCT compared to AP on the outcomes of attention assessments		
	Second objective is to test the effects of a combined cognitive intervention that incorporates CaCT and AP		
3 What: materials	Ca CT (RehaCom, Hasomed Inc., Germany, http://www.hasomed.de) will be conducted in the study. Patients will sit in front of the RehaCom system. The training program will be displayed on the computer screen and they also can hear the sound feedback from the audio system. According to different training programs, patients will press a special RehaCom keyboard with large buttons to react	Acupuncture needle, which is single use, φ 0.35 × 40 mm, will be used for acupuncture treatment. The angle of insertion is approximately 10°–20° (between needle and scalp), the needle should be inserted to a depth of approximately 0.3–0.5B-cun	For the combined group, patients will receive AP and CaCT combined, i.e. the CaCT will be performed while the needles are inserted

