### Statistical methods

All allocated subjects will be analysed with the available data, i.e. on the basis of intention-to-treat (ITT). The last observation carried forward method will be applied in case of missing data.

A significance level of 95 % (two sided *p* values alpha <0.05) will be used. After examining the data for normality (the Kolmogorov-Smirnov test) the outcome measures will be analysed using ANOVA (assuming normal distribution) or Kruskal-Wallis (nonparametric test). Demographic characteristics and other baseline values will be described using descriptive statistics for each group. Significant group interactions will be analysed post hoc. The Bonferroni method will be used to appropriately adjust the overall level of significance for multiple outcomes. A statistician blinded to study groups will conduct statistical analysis.

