Given its small sample size, the pilot study will mainly produce results to provide estimation of large-scale study sample sizes and test the feasibility of the international multicentric study design and its management. A further limitation of the study is the distinction of effects caused by the conventional training as opposed to the experimental interventions. However, the primary aim of the study is a parallel comparison of three experimental interventions rather than comparison to conventional therapy. Hence, no control group receiving no experimental intervention was included for methodological and ethical reasons. This allowed the same amount of time spent with a therapist in all intervention groups. That is deemed as an important measure to prevent bias, particularly when patients cannot be blinded to interventions, as it exposes each group to the same amount of potential placebo effects [45].

The ACoTrain study intends to assess stroke patients of very different cultures (Asia and Europe). Great care has been taken to select cross-culturally adapted and validated assessments to allow pooling of the final data. The assessments are designed to measure the same construct, independent of cultural, educational, or lingual differences. Further, patients in early stroke rehabilitation often present with impairments in other areas than cognition. When assessing cognition, however, these impairments may confound the outcomes, as the task at hand cannot be isolated from other motor and cognition functions. Effects of motor disabilities, impaired perception (e.g. visual deficits, reduced proprioception), or other cognitive defects (e.g. memory) and lack of motivation can limit the interpretability of attention assessments [46]. The eligibility criteria were carefully selected to exclude such confounding factors. To further promote internal validity of the assessments, trained and experienced neuropsychologists will educate all assessors accordingly. To achieve this, a series of assessment training workshops for all personnel involved in the study have been held twice prior to the beginning of the study (March 2014 and August 2014 in Germany and China respectively).

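### The main objective is CaCT versus AP, but the Background aims omit it and the analysis commits to pairwise comparison only after a significant three-group result

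*Protocol article*

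**What the plan says.** **Objectives.** The Abstract (Background) states: "The main objective of this pilot study is to evaluate the effects of computer-assisted cognitive training compared to acupuncture on the outcomes of attention assessments". It places the combined intervention second. The Abstract's Discussion paragraph repeats the CaCT-versus-AP focus. Table 2, item 2, has the same order: "Main objective is to evaluate the effects of computer-assisted cognitive training CaCT compared to AP on the outcomes of attention assessments". The third paragraph of the main Discussion also gives the aims as CaCT against AP, then the combination.

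The last paragraph of the main Background differs. Its first aim is "to observe the effect of acupuncture combined with RehaCom training on cognitive dysfunction". Its second aim is the efficacy of that combination against conventional care plus acupuncture or conventional care plus RehaCom. CaCT versus AP is not among the listed aims.

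**Analysis.** Statistical methods analyses the outcomes by ANOVA or Kruskal-Wallis at two-sided 0.05, with Bonferroni adjustment for multiple outcomes. On what follows it says only: "Significant group interactions will be analysed post hoc". It promises descriptive statistics for demographic and baseline values. It names no pairwise contrast, effect estimate or confidence interval.

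**Purpose.** The Sample size section says the numbers are too small for a full-scale study but should support effect estimation and planning. It adds: "The results will be used to compute sample size and conduct a power calculation to plan the full-scale follow-up study".

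**The concern.** There are two linked problems.

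First, the formal aims paragraph does not contain the question that the Abstract and Table 2 call the main one. Anyone writing the detailed analysis from this article could take the primary contrast from either place.

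Second, the analysis is built as a significance filter, while the pilot's declared product is estimates. A three-group omnibus test does not address CaCT versus AP specifically. If pairwise work follows only a significant result, the contrast that answers the main objective is either not committed to or is examined in a subset of trials selected for large observed differences. The first outcome leaves the follow-up trial without its main planning input. The second gives it an inflated one.

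**Working it through.** **Inputs from the article.** Three clinics with 20 patients each and 1:1:1 allocation (Sample size; Abstract, Methods/Design). Two-sided alpha 0.05 and a three-group test (Statistical methods).

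**Reproducing the plan's figure.** 3 × 20 = 60 in total, and 60 / 3 = 20 per arm. The article gives no power, effect size or SD, so there is nothing further to reproduce.

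**Assumptions.** The article gives no effect size, so the true CaCT-AP difference d is set at 0.3, 0.5 or 0.8 SD. The ACT mean is set either midway between the two single arms or equal to the better one. Outcomes are taken as normal with equal variances, analysed by one-way ANOVA with 2 and 57 degrees of freedom (critical F = 3.16).

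**Step 1: how often the omnibus test is significant.** Power comes from the noncentral F distribution with λ = 20 × Σ(mean − grand mean)².

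- ACT midway: λ = 20 × d²/2. At d = 0.5 this is 20 × 0.125 = 2.5.
- ACT equal to the better arm: λ = 20 × 2d²/3. At d = 0.5 this is 20 × 0.1667 = 3.33.

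| True d (SD) | ACT midway | ACT equal to better arm |
|---|---|---|
| 0.3 | 12% | 15% |
| 0.5 | 26% | 34% |
| 0.8 | 59% | 72% |

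At d = 0.5 the follow-up comparison is thus not triggered in about 66% to 74% of trials. The article does not say how many outcomes the Bonferroni adjustment covers. If it covered the four TAP procedures (alpha 0.05/4 = 0.0125), the omnibus test would be significant in 12% to 16% of trials at d = 0.5.

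**Step 2: what the CaCT-AP estimate looks like when follow-up is triggered.** This was simulated with at least 100,000 trials per setting and a true d of 0.5.

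- All trials: mean estimate 0.50 SD.
- Trials with a significant omnibus test, ACT midway: 0.85 SD.
- Trials with a significant omnibus test, ACT equal to the better arm: 0.77 SD.

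The inflation is therefore 0.77/0.50 = 1.5-fold to 0.85/0.50 = 1.7-fold.

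**Step 3: does a significant omnibus result answer the main objective?** Not by itself. With CaCT equal to AP and ACT alone better by 0.8 SD, λ = 20 × (2/3) × 0.64 = 8.53, and the omnibus test is significant 72% of the time with no CaCT-AP difference present.

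**Step 4: what reporting the contrast every time would give.** The half-width of the 95% interval for CaCT minus AP is t(0.975, 57) × √(2/20) = 2.002 × 0.316 = 0.63 SD. The interval is wide, but the estimate is unselected and always available.

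**The case against.** The strongest reply is that most of the article agrees with itself and that the rest is left to documents not shown.

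- **The objectives.** A reader might infer three rival main questions, because the Discussion also says "the primary aim of the study is a parallel comparison of three experimental interventions rather than comparison to conventional therapy". That reading is not supported. The sentence explains why there is no arm with conventional therapy alone and need not rank the contrasts. Four other places agree on CaCT versus AP. The real outlier is the Background aims paragraph, and there the objection fails, because an incompatible list of aims is printed.
- **No estimate at all.** A reader might infer that the main contrast will go unreported after a non-significant test. The article does not say so. Group results could be reported anyway, and a separate analysis plan could add the contrast. What stands is narrower: the article itself commits to no such estimate, and the one follow-up rule it states depends on significance.
- **The wording of the gate.** A one-way ANOVA or Kruskal-Wallis test has no interaction, so the phrase may mean a group effect or, since outcomes are measured at T0 and T1, group by time. On either reading significance is the condition for follow-up.
- **The procedure.** An omnibus test followed by pairwise tests is a recognised approach for testing. That is granted. The mismatch is with a pilot meant to estimate.
- **The size of the effect.** A reader might infer that a non-significant omnibus result is likely under any plausible effect. It is not: at 0.8 SD the test is significant in 59% to 72% of trials. With AP, CaCT and ACT means of 0, 0.5 and 0.75 SD it is significant in 55%. Nor should a loss from Bonferroni correction over the three pairs be charged to the plan, which states that correction for outcomes only. The general imprecision of a 20-per-arm estimate is ordinary sampling error and would remain after the fix.

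**Conclusion.** The point holds in this limited form and should be fixed. The Background aims omit the contrast that the Abstract, Table 2 and the Discussion make the main objective. Statistical methods commits to pairwise comparison only after a significant group result, which works against the pilot's purpose of estimating effects for planning.

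Both statements rest on the text. The figures only illustrate the size, and they depend on the assumed effect, the assumed ACT mean, normality and 20 complete patients per arm. For an exploratory pilot that acknowledges its limited size, this is a correctable weakness and does not invalidate the design.

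**What to change.** 1. In the last paragraph of the Background, restate the aims in the order used in the Abstract, Table 2 and the Discussion: CaCT versus AP first, the combination second.
2. In Statistical methods, prespecify CaCT minus AP as the primary contrast, with ACT minus CaCT and ACT minus AP as secondary contrasts. Report all three with 95% confidence intervals whatever the omnibus result.
3. Replace the reference to group interactions with the effect actually meant.

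The cost is one reworded paragraph and one added contrast statement, with no new patients, data or procedures. The drawback is that the intervals will be visibly wide, about ±0.63 SD for CaCT minus AP. That is a fair picture of what 20 per arm can show.

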### Patient safety

Adverse effects attributable to the RehaCom therapy may include mental fatigue or headache. Symptoms usually resolve in patients as they progress with therapy and become more familiar with it [39]. Acupuncture may cause discomfort or bruising at the sites of needle insertion, nausea, or feeling faint after each treatment.

Any medical occurrence after inclusion, which is not necessarily caused by the intervention (adverse events, AEs) will be recorded on the individual CRFs and on a progress protocol. This report will be sent to the ethics committee and the sponsor once a year as a safety report.

Serious adverse events (SAEs) will be reported to the sponsor immediately and all participating clinics will be informed by the sponsor. It is the responsibility of each study centre to inform the local ethics committee within 7 days.

### Quality control

To ensure that treatments are of a high standard and delivered in accordance with the trial protocol, clinicians involved in assessments, treatment or training will have to provide a proven record of at least 3 years of clinical experience and certified training or education in related fields of rehabilitation or research. The acupuncture will only be performed by professional physicians with specific training in TCM and a minimum of 2 years of experience. They will participate in a 3-day training course in the standard operating procedures (SOPs) provided by the author of the mutualised protocol and the standard operation videos. In this training course, the protocol will be explained and practiced during exercises and role plays.

## Discussion

Cognitive impairments, such as, memory, executive function, and attention deficit frequently occur in stroke patients, though sometimes, attentional deficit is the only cognitive impairment apparent [40]. Sustaining attention is a prerequisite of motor relearning [41], which is essentially the mechanism of functional recovery after stroke [42]. The traditional neurocognitive strategies [43] used to improve attention deficit after stroke often result in incomplete resolution, and thus, more effective adjuvant strategies are needed.

Acupuncture focuses on the global cognitive function from the holistic conception of TCM, while the RehaCom cognitive training concerns the specific impaired cognitive functions, which need to be trained from the viewpoint of symptomatic treatment. However, the cognitive impairment after stroke is so complex that it needs an integrated method.

The aims of our study are to compare CaCT and AP efficacy in terms of attention improvement after stroke and to investigate the potential effect of a combination of both (ACT). The participants will have the study treatment added to their existing rehabilitation program and will be assessed for changes in attention (intensity, selectivity, and divided attention) at 4 weeks.

Although CaCT and AP both have shown to have beneficial effects on overall cognition in various studies, they have not been compared directly and for specific attentional performance. This is the first study of its kind that assesses attention-specific outcomes for both methods and not only compares the methods but also advances into new approaches where two methods well accepted in two very different cultures are combined to complement one another. The multicentric approach allows more generalisable interpretation [44] of the results and the usage of standardised and cross-culturally adapted assessments allows comparison and pooling of all study data coming from different trial centres.

Given its small sample size, the pilot study will mainly produce results to provide estimation of large-scale study sample sizes and test the feasibility of the international multicentric study design and its management. A further limitation of the study is the distinction of effects caused by the conventional training as opposed to the experimental interventions. However, the primary aim of the study is a parallel comparison of three experimental interventions rather than comparison to conventional therapy. Hence, no control group receiving no experimental intervention was included for methodological and ethical reasons. This allowed the same amount of time spent with a therapist in all intervention groups. That is deemed as an important measure to prevent bias, particularly when patients cannot be blinded to interventions, as it exposes each group to the same amount of potential placebo effects [45].

The ACoTrain study intends to assess stroke patients of very different cultures (Asia and Europe). Great care has been taken to select cross-culturally adapted and validated assessments to allow pooling of the final data. The assessments are designed to measure the same construct, independent of cultural, educational, or lingual differences. Further, patients in early stroke rehabilitation often present with impairments in other areas than cognition. When assessing cognition, however, these impairments may confound the outcomes, as the task at hand cannot be isolated from other motor and cognition functions. Effects of motor disabilities, impaired perception (e.g. visual deficits, reduced proprioception), or other cognitive defects (e.g. memory) and lack of motivation can limit the interpretability of attention assessments [46]. The eligibility criteria were carefully selected to exclude such confounding factors. To further promote internal validity of the assessments, trained and experienced neuropsychologists will educate all assessors accordingly. To achieve this, a series of assessment training workshops for all personnel involved in the study have been held twice prior to the beginning of the study (March 2014 and August 2014 in Germany and China respectively).

## Trial status

Ongoing recruitment.

## Abbreviations

ACoTrain: ACT, intervention that incorporates CCT and AP
AEs: Adverse events
AP: Acupuncture
BL: Baseline
Ca CT: Computer-assisted cognitive training
DCC: Data Control Centre
e-CRF: Digitalised Case Report Form
EQ-5D: EuroQol Questionnaire
ITT: Intention-to-treat
KAP: Short aphasia test
MBI: Modified Barthel Index
MoCA: Montreal Cognitive Assessment
NIH-SS: National Institute of Health Stroke Scale
p-CRF: Paper Case Report Form
RCTs: Randomised controlled trials
SAEs: Serious adverse events
SOPs: Standard operating procedures
T2B: Test des Deux Barrages
TAP: Test for Attentional Performance
TCM: Traditional Chinese Medicine
TIDieR: Template for Intervention Description and Replication checklist and guide
TMT: Trail Making Test
